***Claim 1: Conjunctions of conversational behaviors across modalities better***
***predict IBS*. **Understanding how social bonds among peers are reflected in IBS requires the integration across the conversational modalities: verbal, non-verbal, and paraverbal, rather than looking at one single conversational modality or behavior (such as eye gaze).***Claim 2: IBS and rapport evolve similarly across time*. **We use Dynamic Time Warping to quantify the temporal similarity between the two representations of social connectedness, through dyadic measures at the neural and psychological level.***Claim 3: IBS Granger-causes reciprocal conversational behaviors*. **Beyond temporal similarity, we expect that IBS is a precondition of successful dyadic conversational behavior and thus the emergence of rapport.***Claim 4: Not all rapport is productive*. **We introduce the notion of “productive rapport”; that is, rapport that leads to learning gains in educational tasks, in contrast to unproductive rapport that is detrimental to learning. We therefore run analyses that examine whether there is a inverted U-shaped curve between rapport-building and performance.***Claim 5: Rapport-building is a process that takes time*. **Rapport is rarely built in a 1-h session, and so we argue that a study design must illuminate the time course of rapport at both the time scale of an hour during a single interaction, and of several weeks in a longitudinal design.***Claim 6: Brain regions evolve with age*. **It is well-known that the brain evolves across the period of middle childhood and beyond (Lebel and Beaulieu, 2011). We argue that with age we will find more reciprocal conversational behaviors, as children become more able to participate in interpersonal synchrony, and increasingly able to develop abstract shared mental representations with others. We predict that this will lead to greater IBS, and a progressive shift in activation from rTPJ to PFC.

Bringing these axes together we predict that we will find stronger and more generalized IBS where conversational behaviors (verbal, non-verbal, and paraverbal) are reciprocal. That is, in cases of mutual eye gaze and mutual smiles, reciprocal self-disclosure, and entrainment (sometimes called alignment) where the pattern of behavior is increasingly similar between members of a dyad, such as increasingly similar speech rate. We predict that these patterns of dyadic behavior will be followed by increased IBS and that, in turn, this will allow us to distinguish between productive and unproductive rapport on the basis of IBS that follows dyadic behavior. That is to say, IBS will be present in more regions of interest, and will be stronger, when it co-occurs with high rapport that accompanies (and just precedes) learning gains.

Here, due to its non-invasive nature, high safety profile, reduced sensitivity to participants' motion, and higher spatial resolution than EEG, the fNIRS technique can play an important role (Providência and Margolis, 2022). Its reduced sensitivity to movement makes it ideally suited to investigate the naturalistic phenomena that make up social interaction (Pinti et al., 2020), and particularly social interaction among children, who may find it difficult to stay completely still. While EEG captures responses to individual events at a high temporal granularity (single syllables, articulation of the face), fNIRS integrates over these to reveal the different brain region that are more or less active on the timescale of seconds, and therefore allows us to focus on overall task components, rather than events at the sensory modality level of resolution.

An earlier study conducted by Rabinowitch and Knafo-Noam (2015) found that ratings of closeness were higher for children who participated in a synchronous finger tapping exercise, a result thought to illustrate the positive effects of synchronous (non-conversational) interaction in children, but given the increased focus in neuroscience on actual social interaction, and the tools available to do so, it is time to study IBS in child dyads engaging in actual social interaction, with an eye toward better understanding and better implementation of supporting technologies.

In what follows we therefore propose a novel study and concomitant methodology to address some of the questions raised by prior work, and to adduce evidence for the claims laid out above. We have adapted an ecologically valid interactive task used in our prior work (Finkelstein, 2018; Cassell, 2022), attractive to children across middle childhood, that can be carried out by one child (solo phase), and by dyads (collaborative phase), while attached to fNIRS apparatus. The task has variations that allow children to engage several times over a period of weeks, each time with a solo phase and a collaborative phase, and calling on slightly different skills each time, but demanding the same amount of effort. In a subsequent study, the same tasks can be carried out by a child-virtual peer dyad (as has been demonstrated in our prior work). Because the results will also inform the design of that VP, which will interact with its child interlocutor through a computer screen, all phases of the child-child experiment take place via videoconference. This also facilitates matching children with strangers of the same age, so that all evaluations of rapport are based on interactions between children who have never before met. A recent study of interaction across videoconference has shown that neither mimicry nor levels of trust are significantly different from face-to-face conditions (Diana et al., 2023). However, other studies suggest that remote interactions exhibit reduced levels of IBS compared to in-person interactions (Schwartz et al., 2022). This observed reduction might be associated with the reduced turn-taking found in Zoom interactions (Balters et al., 2023), and is postulated to be due to a decrease in the intensity of face processing and social interaction (Zhao et al., 2023). Nevertheless, assessing IBS in dyads communicating via videoconference remains feasible (Wikström et al., 2022) and important, given the increased presence of videoconference interactions in everyday life.

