### 5.2 fNIRS data pre-processing

For each subject, raw data will be visually inspected for evidence of artifacts that would result in poor data quality. Pre-processing will be carried out by MNE-NIRS, a dedicated Python library for pre-processing fNIRS data (Luke et al., 2021). To further enhance data quality, for each source-detector pair, the impact of systemic physiological factors will be attenuated by performing short-channel regression using the temporally embedded Canonical Correlation Analysis (von Lühmann et al., 2020). Raw intensity values will be converted into optical density values and then motion-corrected using temporal derivative distribution repair (Fishburn et al., 2019). The scalp coupling index (SCI), a measure of signal strength between the optodes and the scalp (Pollonini et al., 2014), will then be calculated for each of the 42 channels for the entire experiment. Any channel with an SCI value lower than 0.8 will be excluded from subsequent analysis (Pollonini et al., 2016). For the subsequent dyadic neural synchrony calculations (described further below), only shared channels with sufficient SCI will be used. Remaining data will then be converted into hemoglobin concentration values using the modified Beer-Lambert law (Baker et al., 2014). Data will be filtered in order to remove heart rate and respiration artifacts by applying a band-pass filter between 0.01 and 0.5 Hz (Yücel et al., 2021). Both oxygenated hemoglobin (HbO) and deoxygenated hemoglobin (HbR) will be analyzed, as HbO exhibits greater sensitivity to changes in cerebral blood flow (Jiang et al., 2012), while NIRS data acquired during verbal communication is most accurately represented by the HbR signal (Zhang et al., 2017), since speaking can influence end-tidal CO2 blood levels (Scholkmann et al., 2013).

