For each dyad, we will obtain IBS values for each 30 second epoch and each ROI pair. We will also compute the average IBS across each 8–10 min phase of the experiment. In total, we will thereby obtain IBS values for each dyad, from each ROI, for the entire phase and for each 30-second epoch within that phase. To best capture the IBS evoked by social interaction, we normalize the values of the social phase by computing a Z-score, i.e., removing the average value of the solo phase and dividing by the standard deviation. This process is repeated for each dyad. To compare the difference between phases, then, we run a general linear model (GLM). Normalized IBS values are entered as the dependent variable with interactive phases (i.e., collaboration and discussion) and the interaction effect of ROIs (six per dyad) as fixed factors. To assess whether the observed neural activity is most likely due to exchanges between the children, as opposed to being primarily driven by the content of the task, we will also generate random pairings by calculating IBS with false dyads (the child's time-series paired to the time-series of another child coming from a different dyad during the same phase). We will create multiple such random pairs to generate the distribution of IBS expected under the null hypothesis (H0) (Nguyen et al., 2021a). The values of the actual real pairs will then be compared to these H0 distributions, thus providing an empirical *p*-value. An example of this analysis is illustrated for the feasibility study in Figure 5B. We will also generate a more conservative intra-pair comparison based on temporally shuffled behavior. In this case, the participants stay the same but the epochs are randomized to generate false dyads (Ayrolles et al., 2021).

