### 5.3 Behavioral annotation

We argued above that it is not sufficient to focus on one single conversational behavior, nor one single modality of conversational behaviors, in order to understand the ways in which the behaviors of social interaction are related to IBS. Here we describe how we acquire the multimodal data. Conversation is influenced by the situational context (e.g., classroom vs. playground, brainstorming vs. class presentation), and by the interlocutor (e.g., adult vs. child, stranger vs. friend or family member). These differences underscore the importance of rigorous annotation, including using automatic extraction based on advances in signal processing to allow efficient treatment of large amounts of data, as well as hand annotation using coding manuals tested and normed for the culture and age group in question.

In terms of the automatic extraction of nonverbal behavior, we will employ OpenFace, a widely-used open-source computer vision framework that utilizes action units (AUs) to detect facial landmarks, allowing us to detect facial expressions in video (Baltrusaitis et al., 2018). AUs are translated into behavioral features such as smiles. This allow us, for example, to differentiate between the Duchenne or genuine smile and the polite smile (Ekman et al., 1990). We will next perform a manual check on 10% of the data at each age using the ELAN video annotation tool (Wittenburg et al., 2006) to ensure that the behaviors are correctly annotated by the software. We have conducted such checks in the past, and have found alignment between high inter-rater reliability hand annotation and OpenFace. If, however, this is not the case for these data for any reason, we will fine-tune the software with the annotated data to ensure alignment and then retest on a second sample of 10%. Second order behaviors (e.g., mutual smiles) will then be automatically extracted. Assessment of eye gaze in the videoconference-mediated conversations will be achieved using the framework developed by Tran et al. (2022) applied to the raw eye gaze data generated by OpenFace. This application enables the extraction of eye gaze direction employing a dynamic clustering algorithm. As with facial expression, we will then automatically extract the second-order behavior of mutual eye gaze.

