### 6.1 Claim 1: conjunctions of conversational behaviors across modalities better predict IBS

We argue that focusing on a single conversational behavior (such as eye gaze) under-estimates the complex interplay among modalities in their relationship to neural synchrony. To adduce evidence for this claim we will leverage Long Short-Term Memory (LSTM) networks to predict IBS on the basis of temporal sequences of behavioral data (see Table 1 for further details on the behavior types and variables). Since conversational behaviors are likely to lead to IBS with a certain lapse of time, we insert a 1 to 10 second time lag between the sequences of conversational behaviors and the IBS (Chang et al., 2022). The dataset will be structured into sequential behavioral data over time, each associated with a 30-second interval IBS value and normalized through a Min-Max scaling technique, ensuring consistent proportions across all features, while preserving the original distribution of the data.

**Table 1 T1:** Data sheet.

**Level of data type**	**Modality**	**Dyadic status**	**Specific variables**	**Notes**
Conversational Behavior	Verbal	Non-reciprocal	◾Self-disclosure	Number of behaviors per 30 second epoch.
			◾Reference to shared experience	
			◾Praise	
			◾Teasing	
		Reciprocal	◾Mutual self-disclosure	
			◾Mutual reference to shared experience	
			◾Mutual teasing	
	Paraverbal	Non-reciprocal	◾Pitch shift	
			◾Shift in speed of speaking	
			◾Shift in loudness	
		Reciprocal	◾Mutual pitch shift	
			◾Mutual shift in speech rate	
			◾Mutual shift in loudness	
	Nonverbal	Non-reciprocal	◾Smile	
			◾Head nod	
			◾Gaze at other person	
		Reciprocal	◾Mutual smile	
			◾Mutual head nod	
			◾Mutual eye gaze	
Rapport State		Rapport rating (1–7) for each 30 second interval for each dyad		
Educational Performance		Every week	Task 1–3, week (with x = 1–6)	◾Number of hypotheses per weekly 8–10 min read-out
				◾Number of pieces of evidence per 8–10 min weekly read-out
IBS				◾Right hemisphere ROIs

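### For mutual smiles and head nods, neither null comparison can tell residual motion artefact shared by partners from neural synchrony, and a motion-adjusted sensitivity analysis is needed

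*Protocol article*

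**What the plan says.** Section 3 (Framework) expects stronger and more widespread IBS where behaviours are reciprocal, naming mutual smiles among the examples, and predicts that "these patterns of dyadic behavior will be followed by increased IBS". It supports the choice of fNIRS with the statement "Its reduced sensitivity to movement makes it ideally suited to investigate the naturalistic phenomena that make up social interaction". Table 1 (Section 6.1) lists nine reciprocal variables: three verbal, three paraverbal and three non-verbal. The non-verbal ones are mutual smile, "Mutual head nod" and mutual eye gaze.

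Section 5.2 plans visual inspection, short-channel regression (aimed at systemic physiology), signals "motion-corrected using temporal derivative distribution repair" (TDDR), exclusion of channels with a scalp coupling index (SCI) below 0.8, and a 0.01–0.5 Hz band-pass filter.

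Section 5.2.2 computes wavelet coherence over 0.01–0.15 Hz and compares real pairs with two nulls. In the first, false dyads are formed with "the child's time-series paired to the time-series of another child coming from a different dyad during the same phase". In the second, described as more conservative, "the participants stay the same but the epochs are randomized to generate false dyads". The social phase is also standardised against the solo phase.

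Section 5.3 already plans video processing with a tool that "utilizes action units (AUs) to detect facial landmarks, allowing us to detect facial expressions in video".

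**The concern.** Reduced sensitivity to movement is not absence of it, and the plan itself corrects for motion. A mutual smile or nod moves both children's heads or faces at about the same moment. Whatever artefact survives cleaning can then appear in both recordings together, and coherence does not distinguish a shared artefact from a shared neural signal.

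The null comparisons are the plan's evidence that IBS reflects the exchange between partners. If shared motion passes through them, a link between smiles or nods and IBS could be reported as neural synchrony when part of it is movement. Section 9 already reads feasibility data in this way: it takes the authentic-versus-random contrast as evidence of social interaction, and notes that one dyad's smiles coincided with raised IBS. Shared motion could contribute to both patterns; nothing in the article shows that it did. The Limitations (Section 10) do not mention it. Section 7 would carry behaviours identified as effective into the virtual peer.

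**Working it through.** **Step 1: what each planned step can do.** Write the two partners' cleaned signals as x₁ = n₁ + a₁ and x₂ = n₂ + a₂, where n is the neural part and a the residual artefact. Wavelet coherence is |S(W₁W₂*)|² / [S(|W₁|²)·S(|W₂|²)], with S a smoothing operator. If n₁ and n₂ are independent of each other and of the artefacts, the expected cross-term is that of a₁ and a₂ alone.
- Real pair: a₁ and a₂ come from the same mutual movements, so the cross-term is not zero.
- False dyad: a₁ and a₂ come from movements in different conversations, so their alignment is lost.
- Shuffled epochs: same children, different moments, so alignment is lost again.
- Solo standardisation: subtracting one constant and dividing by another cannot remove an association that arises within the social phase, and the solo phase contains no mutual behaviour.
- The 1–10 s lag in Section 6.1 is shorter than the 30 s epoch over which IBS is averaged, so it does not clearly separate an immediate artefact from a later response.

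**Step 2: size, real pairs against the nulls.** The article gives no artefact size, so this is a simulation with zero neural synchrony.
- From the document: 7.81 Hz sampling, TDDR per child, 0.01–0.5 Hz band-pass, coherence over 0.01–0.15 Hz, 30 s epochs, and a 9-minute phase (within the stated 8–10 min).
- Assumed: 24 dyads; 18 mutual movements per phase (540 s / 30 s = 18, one per epoch); 0.3 s jitter between partners; three artefact shapes (a brief spike, a shift with slow recovery, a slow bump of about 3 s), with amplitudes in neural-signal SDs. Short-channel regression is not included.

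| Artefact, after TDDR | Real | False | Shuffled | Dyads above 95th percentile of false pairs |
|---|---|---|---|---|
| None | 0.41 | 0.42 | 0.39 | 8% |
| Spike, 10 SD | 0.41 | 0.40 | 0.40 | 12% |
| Spike, 5 SD | 0.43 | 0.41 | 0.41 | 42% |
| Shift, 3 SD | 0.46 | 0.42 | 0.39 | 50% |
| Shift, 6 SD | 0.51 | 0.41 | 0.41 | 83% |
| Slow, 1 SD | 0.43 | 0.41 | 0.39 | 33% |
| Slow, 2 SD | 0.53 | 0.41 | 0.40 | 96% |
| Slow, 3 SD | 0.58 | 0.40 | 0.40 | 100% |

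Without TDDR, the 10 SD spikes gave 0.59 in real pairs (100% of dyads) and the 3 SD shifts also 0.59 (100%). TDDR thus removes most of the largest spikes and part of the shifts, but little of the slow movement (2 SD: 0.55 before, 0.53 after). Both nulls stay near 0.4 throughout, so neither absorbs the artefact. With 24 dyads the percentages are coarse.

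**Step 3: size, behaviour against IBS.** A second simulation (150 dyads × 18 epochs, coherence over 0.02–0.15 Hz, no short-channel step) correlated the epoch's mutual-movement count with IBS. It gave r = 0.04–0.10 at 1 SD and r = 0.17–0.28 at 2–4 SD, the latter being 0.17² = 3% to 0.28² = 8% of variance.

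**Step 4: effect of short channels.** A third simulation (60 dyads × 18 epochs, 2–4 SD) used lagged regression on four simulated short channels. This is a simplification of the planned method, which has eight short channels and canonical correlation.
- No short-channel step: r = 0.18–0.27.
- Artefact half shared with the short channels: r = 0.06–0.12.
- Artefact fully shared: r = −0.01 to 0.05.
- No artefact: r = −0.03 to 0.04.

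The short channels protect only as far as the artefact also appears in them, which the article does not establish.

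**Step 5: effect of motion adjustment.** Regressing out a lagged movement trace brought the false r to within 0.03 of zero, except for the largest slow artefact (0.26 to 0.10). With a true delayed response and no artefact, r fell from 0.07 to 0.06 and from 0.21 to 0.14, the latter a loss of (0.21 − 0.14)/0.21, or one third.

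**The case against.** The strongest reply has four parts.

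First, the plan has several layers of cleaning, and every simulated artefact size and shape is an assumption. Nothing in the article says that a child's smile or nod produces slow movements of 2 SD. This stands: the bias may be negligible. It does not show that the nulls would detect the bias if it were there.

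Second, Section 3 claims only reduced sensitivity, in a comparison with EEG, and the false-dyad null is introduced to separate exchange from task content. Both are correct. The sentence is not an error, and the false-dyad null serves its stated purpose. The gap lies in a second alternative explanation, which neither null addresses.

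Third, motion covariates are detail that a condensed article may leave to a fuller document. That would dispose of a bare omission. Here, however, the article sets out the cleaning steps, the nulls and the inference, and for these two variables the stated nulls cannot carry the inference.

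Fourth, adjusting for movement conditions partly on the predictor itself. This stands, and is why the adjustment should not become the primary analysis.

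Two stronger readings are tempting but not supported. A reader might infer that the reciprocal behaviours in general are simultaneous movements. Only smiles and nods, two of nine, clearly are: gaze needs little movement, the other six are verbal or paraverbal, and Section 2 describes reciprocal self-disclosure as sequential. Nods, moreover, enter through Table 1 and are not named in the Section 3 prediction. A reader might also infer that the artefact favours Claims 1 and 3. Claim 1 is about combining modalities, and artefact tied to smiles and nods would favour the non-verbal modality alone; the ablation and SHAP analyses in Section 6.1 would show such dominance, though not its cause. No Granger model was simulated, so the effect on Claim 3 is untested.

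**Conclusion.** The point holds for mutual smiles and mutual head nods. Residual motion shared by partners may survive per-child cleaning, and neither false dyads nor shuffled epochs can separate it from neural synchrony. That much follows from how the nulls are built and needs no assumption about size, only that some shared artefact remains.

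The size in this study cannot be known from the article. Under assumed artefacts and zero true synchrony, it ranges from no material effect (10 SD spikes after TDDR; artefact fully shared with the short channels) to a large false contrast (2 SD slow movements: 0.53 against 0.41, with 96% of dyads above the null's 95th percentile). The large results come from simulations without short-channel regression, the SCI cut-off or visual inspection. This calls for a sensitivity analysis and a qualified interpretation; it does not invalidate the pipeline.

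**What to change.** Keep the primary pipeline and pre-specify the following.

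1. From the OpenFace output planned in 5.3, derive a head/face movement trace for each child (for example, frame-to-frame landmark displacement), aligned to the fNIRS recording through the event timings described in Section 6.
2. Repeat the real-versus-null contrast, and the behaviour–IBS analyses for smiles and nods, either with lagged motion regressed out or with epoch motion as a covariate. Report adjusted and unadjusted results side by side.
3. Report whether the reciprocity effect also holds for mutual eye gaze and for the verbal reciprocal behaviours, which need little simultaneous head movement.
4. Attribute a smile–IBS or nod–IBS link to neural synchrony only if it persists in steps 2 and 3.
5. State in 5.2.2 and in the Limitations that the two nulls do not control for time-locked shared motion.

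The cost is analysis code and reporting; no new data are needed. The downside is that adjustment removes part of any true response time-locked to movement (in simulation, r from 0.21 to 0.14) and may leave some artefact behind (r of 0.10 in the worst case). A link that weakens under adjustment is therefore inconclusive and does not refute synchrony.
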